### Interventions

For intervention group 1, intra-operative intravenous TXA is administered within 30 min before knife to skin (KTS) or application of a tourniquet plus oral TXA at 2 h, 10 h, 18 h and 26 h post KTS. Each oral dose should be given within a 2 h window but not earlier than the planned time point for the first dose. Patients with renal impairment will receive a reduced dose dependent on their pre-operative serum creatinine as per Table 1.

**Table 1 Tab1:** Study drug administration

	Up to 30 mins pre KTS	+ 2 h post KTS	+ 10 h post KTS	+ 18 h post KTS	+ 26 h post KTS
Intervention group 1 Normal creatinine <120 μmol/L	1 g TXA IV	1 g TXA oral	1 g TXA oral	1 g TXA oral	1 g TXA oral
Intervention group 1 High (A) creatinine level 120–249 μmol/L	0.5 g TXA IV	0.5 g TXA oral	0.5 g TXA oral	0.5 g TXA oral	0.5 g TXA oral
Intervention group 1 High (B) creatinine level 250–499 μmol/L	0.5 g TXA IV	–	0.5 g TXA oral	–	0.5 g TXA oral
Intervention group 1 High (C) creatinine level ≥ 500 μmol/L	0.5 g TXA IV	–	–	–	0.5 g TXA oral
Intervention group 2 Normal creatinine level < 120 μmol/L	1 g TXA IV	–	–	–	–
Intervention group 2 High (A) creatinine level 120–249 μmol/L	0.5 g TXA IV	–	–	–	–
Intervention group 2 High (B) creatinine level 250–499 μmol/L	0.5 g TXA IV	–	–	–	–
Intervention group 2 High (C) creatinine level ≥ 500 μmol/L	0.5 g TXA IV	–	–	–	–
Control group 3 – no TXA All creatinine levels	–	–	–	–	–

*IV* intravenous, *KTS* knife to skin, *TXA* tranexamic acid

For intervention group 2, intra-operative intravenous TXA is administered within 30 min before KTS or application of a tourniquet. Patients with renal impairment will receive a reduced dose dependent on their pre-operative serum creatinine.

### Study drug

TXA 100 mg/mL solution for injection and TXA 500 mg tablets are regarded as investigational medicinal products for this study.

The study medication is provided as:Packs containing two 5-mL ampoules of TXA 100 mg/mL solution for injectionPacks containing one 5-mL ampoule of TXA 100 mg/mL solution for injection (for patients with renal impairment)Packs containing eight TXA 500 mg tabletsPacks containing four tablets, two tablets or one tablet TXA 500 mg (for patients with renal impairment)

Packs are labelled with a unique medication pack identification number in accordance with applicable regulatory requirements. On receipt of a study medication request form, signed by an authorised member of the research team, the pharmacy department supplies a number of medication packs to the operating theatre. These are then available for administration to patients according to the treatment allocation specified in the assigned sealed envelope. The medication pack goes with the patient from theatre to ward depending on randomisation.

Drug administration is recorded on the patient’s hospital prescription chart and on their case report form (CRF).

Used and unused medication packs are returned to the site pharmacy department. The site pharmacist is responsible for maintaining complete records of the disposition of all study drugs that are received, dispensed, unused, expired, returned to pharmacy or destroyed. The Northern Ireland Clinical Trials Unit (NICTU) provides a drug accountability record form for this purpose. All investigational medicinal products for this study are sourced, packed and labelled for the trial by Victoria Pharmaceuticals, Belfast Health and Social Care Trust.

TXA is administered by slow intravenous injection or orally at the time points indicated in Table 1 in accordance with the treatment allocation specified in the assigned sealed envelope. There are no relevant concomitant care and interventions that are permitted or prohibited during the trial.

### Safety

The conduct of the trial is overseen by a trial steering committee (TSC). Throughout the trial, the TSC takes responsibility for monitoring and guiding overall progress, scientific standards, operational delivery and protecting the rights and safety of trial patients. Monthly trial management group meetings are held involving the NICTU and members of the research team. An independent DMEC was appointed with responsibility for safeguarding the interests of trial patients. This committee monitors the main outcome measures including safety and efficacy. It also assists and advises the TSC to protect the validity and credibility of the trial. Charters for the TSC, DMEC and the trial management group are held by the NICTU.

The principal investigator or designee records all directly observed adverse events (AEs) and all AEs spontaneously reported by the patient. The principal investigator or designee assesses all AEs for seriousness, causality and severity, and if the AE is related to the study drug, for expectedness.

The AE reporting period for the participant begins upon enrolment into the trial and ends 30 days following the last administration of the study drug. All AEs are assessed by the principal investigator as possibly, probably or definitely related to the study drug and all serious adverse events (SAEs) that occur during this time will be followed until they are resolved or are clearly determined to be due to a patient’s stable or chronic condition or intercurrent illness(es). Reporting follows the regulatory requirements and NICTU standard operating procedures.

For TRAC-24, a SAE is an AE that:results in deathis life-threateningrequires hospitalisation or prolongation of existing hospitalisation (even if only for 1 day)*results in persistent or significant disability or incapacityinvolves a congenital anomaly or birth defectis any other important medical events that carries a real, not hypothetical, risk of one of the outcomes above.

*Hospitalisation is defined as an inpatient admission regardless of length of stay, even if the hospitalisation is a precautionary measure for continued observation. Hospitalisations for a pre-existing condition, including elective procedures that have not worsened, do not constitute an SAE.

### Data collection and management

An electronic CRF is used to collect the data for each study subject. Patient identification on the CRF is through their unique trial identifier, allocated at the time of recruitment. Data coding is carried out at various stages during the study. The electronic CRF is subject to audit by the sponsor. Data integrity and study credibility depend on factors such as ensuring adherence to the protocol and using quality control measures to establish and maintain high standards for data quality. To ensure accurate, complete and reliable data are collected, the NICTU provide training to site staff in the format of investigator meetings and/or site initiation visits. The data are validated and discrepancy reports are generated following data entry to identify discrepancies, such as out of range values, inconsistencies or protocol deviations based on data validation checks programmed into the clinical trial database. Data security and storage follows the data management plan specific to this study, NICTU standard operating procedures and the sponsor’s requirements. The DMEC is convened to carry out reviews of the data at staged intervals during the study.

The dropout rate is expected to be negligible with little or no missing data for the primary outcome measure. Standard approaches will be used to detect patterns in missing data for the other outcomes.

### Statistical and interim analysis

Based on a mean (standard deviation) of 1225 (499) mL of blood loss and a clinically significant difference of 150 mL (12%) between the two TXA groups, originally the trial required 233 participants per group at 90% power and 0.05 level of significance. Due to the proven greater blood loss in control group 3, there were only half this number of participants in this group (*n* = 117). This would result in a total of 1166 participants (583 TKA and 583 THA), as a negligible dropout rate was expected. The clinically significant difference of 150 mL was based on an internal audit of blood loss in primary THA and TKA patients. The audit found that the average calculated blood loss was almost 1500 mL. Based on this and the clinical opinion of the anaesthetists, surgeons, and haematologist involved in the study, a value of 150 mL (10% of the average blood loss) was considered to be clinically significant.

Based on the strong rationale that TXA is effective at reducing blood loss for THA and TKA, a planned interim analysis was performed to compare the control and combined intervention groups to determine whether recruitment to control group 3 should continue. A power calculation determined that a sample size of 98 patients would be required to detect a clinically relevant difference of 450 mL of blood loss between the control and combined intervention groups at the significance level of *p* = 0.01 and 90% power. The analysis was performed separately for THA and TKA participants and also for the combined participants.

Following this interim analysis, the DMEC recommended to the TSC that randomisation to control group 3 of patients recruited should be stopped. A minimum of 932 patients is required with an allocation of 466 (233 TKA and 233 THA) to intervention group 1 and 466 (233 TKA and 233 THA) to intervention group 2. Atogether, 134 patients were randomised to control group 3. Eligible participants are now allocated to intervention group 1 or intervention group 2 with an allocation ratio of 1:1.

Analyses will be on an intention-to-treat basis and at an a priori significance level of *p* = 0.05. Baseline characteristics and outcome measures will be summarised as mean and standard deviation, median and inter-quartile range or numbers and proportions (%) depending on the scale of measurement. For the primary outcome and other continuous outcomes, analysis of variance with contrasts will be used to compare both intervention groups and also the intervention groups combined versus the control group. Analysis of covariance will be used to adjust for baseline and other covariates where appropriate. The chi-squared test will be used to test the difference in the proportions between the groups for the categorical variables. All analyses will be performed for THA and TKA separately and also combined. Subgroup analyses will be performed on the primary outcome measure for THA/TKA, creatinine, age, gender and body mass index. A statistical analysis plan will be written and approved prior to commencement of any analyses.

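### The combined-TXA-versus-control contrast is tested at the end at an unreduced 0.05 after an interim test of the same contrast sized at 0.01, so the stated 5% does not hold for it

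*Protocol article*

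**What the plan says.** All of the relevant text is in the protocol article, mainly under Statistical and interim analysis.

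- **Interim contrast and purpose.** "a planned interim analysis was performed to compare the control and combined intervention groups", "to determine whether recruitment to control group 3 should continue". The required number was calculated for a 450 mL difference "at the significance level of *p* = 0.01 and 90% power".
- **Interim populations.** "The analysis was performed separately for THA and TKA participants and also for the combined participants".
- **Consequence.** The Study design section reports that the committee met after 200 patients, 40 of them controls, and recommended ending randomisation to control. Control recruitment had reached 134 when the change was approved, and the Recruitment and consent section puts total recruitment at that point at 672.
- **Final contrast and level.** For the primary outcome and other continuous outcomes, analysis of variance with contrasts will "compare both intervention groups and also the intervention groups combined versus the control group". The level is general: "Analyses will be on an intention-to-treat basis and at an a priori significance level of *p* = 0.05". All analyses are to be run for THA, for TKA and for both together.

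The article gives no split of the 0.05, no reduced final level for the contrast with control, and no statement that this contrast became descriptive once control was dropped. The primary objective is a different contrast, group 1 versus group 2.

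**The concern.** The contrast examined at the interim is examined again at the end on the same outcome, and the 40 interim controls are among the 134 final controls. If a contrast may be declared positive at either of two looks, using the full 0.05 at the second takes the combined error above 0.05. Even if the interim served only to decide about the arm, its result fixes how many controls enter the final test, so that test is not exactly a 5% test.

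At stake is the accuracy of the error rate attached to the claim that TXA, in either regimen, reduces blood loss compared with none. The article goes beyond leaving a detail open: it states a level that the described design does not keep for this contrast.

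**Working it through.** **Inputs from the article**
- Interim: 40 control, 160 TXA (200 patients, 40 of them controls); level 0.01.
- Final level: 0.05.
- Final controls: 134 as it happened; 2 × 117 = 234 as first planned.
- Final TXA patients: 932 (minimum), or 672 − 134 = 538 if only those randomised alongside controls are used. The article does not say which.

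**Sidedness.** The article does not state it. The main sample size gives a check:

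n = 2 × (499/150)² × (1.960 + 1.282)² = 2 × 11.07 × 10.51 ≈ 232.6, so 233 per group, which is the stated figure.

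A one-sided 0.05 would give 190, so 0.05 is taken as two-sided. Two-sided is assumed for the interim 0.01 as well.

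**Reading A: crossing 0.01 at the interim counts as a rejection.**

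Information = 1/(1/n_control + 1/n_TXA). At the interim this is 1/(1/40 + 1/160) = 32. With t = interim information / final information, the two z statistics under no effect are bivariate normal with correlation √t, and

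overall error = 1 − P(|Z1| ≤ 2.576 and |Z2| ≤ 1.960).

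| Final control v TXA | Final information | t | Overall error | Final level that restores 0.05 |
|---|---|---|---|---|
| 134 v 538 | 107.3 | 0.298 | 0.0567 | 0.0430 |
| 134 v 932 | 117.2 | 0.273 | 0.0570 | 0.0428 |
| 234 v 932 | 187.0 | 0.171 | 0.0580 | 0.0418 |

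A simulation of 20 million trials followed the actual path: control stops at 134 if the interim crosses 0.01 and otherwise continues to 234. It gave 0.0580. The ceiling, if the looks were independent, is 1 − 0.99 × 0.95 = 0.0595.

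If only a TXA benefit could count at the interim, half of the excess remains: about 0.0535 to 0.0540.

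**Reading B: only the final test supports a claim.**

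In the same simulation, 30.2% of the trials that crossed at the interim and stopped control at 134 were also significant at the end. The others no longer count:

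0.0580 − 0.01 × (1 − 0.302) = 0.0580 − 0.0070 = 0.0510.

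**Each joint separately.** Assuming the interim split evenly, 20 v 80 per joint, against a planned 117 v 466: 16/93.5 = 0.171. This is the same fraction as the pooled plan, so the error is again about 0.058 for each joint.

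**Why 0.04 is enough.** An error requires either an interim crossing (probability 0.01) or, without one, a significant final test at the planned size (at most 0.04). The sum is at most 0.05 whatever the information fraction, under either reading.

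**The case against.** The best defence is that 0.01 appears only as an input to the interim power calculation. The stated purpose was a decision about the control arm, made by the committee together with a review of safety data. No sentence says that efficacy would be declared at p < 0.01. This stands: it is why the lower figure of 5.1% must be given beside 5.7 to 5.8%. It does not bring the rate back to 0.05.

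A second defence is that handling of alpha for a supporting contrast belongs in the analysis plan or the committee's charter, neither of which is shown. Either may contain an adjustment. But the article sets 0.05 for its analyses immediately after describing the interim, and a plan that followed it literally would carry the unadjusted level forward.

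Three stronger readings are tempting and are not supported:

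- A reader might infer that any of the three interim looks could trigger rejection, giving about 7.0% overall. That mixes THA-only and TKA-only crossings with a pooled final test. A crossing in one joint does not reject the pooled hypothesis, and the article does not say that any one look sufficed.
- A reader might infer that a 95% interval with wrong coverage is planned. The section mentions no confidence interval.
- A reader might infer that the primary result is compromised. Group 1 versus group 2 was not part of the interim test as described.

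**Conclusion.** The point holds, at small size. For combined TXA versus control on 48 h blood loss, the stated 0.05 is exceeded by 0.7 to 0.8 percentage points if an interim crossing counts as a rejection, and by about 0.1 if only the final test counts with control stopped at 134. These figures assume two-sided tests and negligible dropout, which the article expects. They do not depend on the SD used to size the interim, which the article does not give.

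The contrast is a supporting one. The difference sought at the interim was 450 mL and the article already treats greater loss without TXA as proven, so the conclusion is unlikely to change. What needs correcting is the error rate attached to it.

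**What to change.** In the analysis plan:

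1. Test combined TXA versus control on 48 h blood loss at a two-sided final level of 0.04 (0.05 − 0.01). The exact value is 0.042 to 0.043, depending on the final numbers; 0.04 avoids that dependence.
2. Use the same level for the separate THA and TKA versions of this contrast.
3. If an interval is reported for it, make it match the level (96% for 0.04).
4. Report all three interim looks (THA, TKA, combined) and state which one the documents written before the interim made decisive. If none did, say so. Choosing one now, after the result has been acted on, would control nothing.
5. Keep 0.05 for group 1 versus group 2.

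The cost is a few lines of text and a slightly stricter test on a supporting contrast: the critical value rises from 1.960 to 2.054, so a matching interval is about 5% wider (2.054/1.960 = 1.048). No extra patients are needed, and the primary comparison loses no power.

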### Primary outcome measure

The primary outcome measure is the total calculated volume of blood loss, in millilitres, at 48 h. This is calculated indirectly, from a series of equations [20, 21, 29].

The first equation determines the patient’s blood volume in litres:$$ \mathrm{PBV}=\left({k}_1\times {h}^3\right)+\left({k}_2\times w\right)+{k}_3, $$

where

PBV = patient’s blood volume (L),

*h* = height (m),

*w* = weight (kg),

*k*_1_ = 0.3669 for men and 0.3561 for women,

*k*_2_ = 0.03219 for men and 0.03308 for women

and

*k*_3_ = 0.6041 for men and 0.1833 for women.

The second equation determines the volume of red blood cells lost in the period from immediately before the operation to 48-h post operatively. Note that PBV should be converted to millilitres prior to calculation of RBC.$$ \mathrm{RBC}=\mathrm{PBV}\times \left({\mathrm{Hct}}_{\mathrm{pre}\hbox{-} \mathrm{op}}-{\mathrm{Hct}}_{\mathrm{post}\hbox{-} \mathrm{op}48\mathrm{h}}\right), $$

where

RBC = red blood cell volume loss (mL),

Hct_pre-op_ = pre-operative haematocrit

and

Hct_post-op 48h_ = post-operative haematocrit.

The third and final equation converts red cell volume loss into whole blood volume loss. We selected the Gross formula for this [29] and adapted it to incorporate transfusions as per the Mercuriali formula [21].

To convert red blood cell volume loss into total blood volume loss, the RBC must be divided by the average Hct. In addition, volume of transfused blood must be taken into account. An average unit of blood has a volume of 280ml with an Hct of 0.6, which is the red cell equivalent of 168mls with an Hct of 1.0. As this is diluted by patient blood volume, the value must again be divided by average Hct.

The Gross formula (adapted assuming an average Packed Red Cells (PRC) unit is 280 mL with a Hct of 0.6) is$$ \mathrm{Total}\kern0.5em \mathrm{volume}\kern0.5em \mathrm{loss}=\frac{\mathrm{RBC}}{{\mathrm{Hct}}_{\mathrm{avg}}}+\left(\left(\mathrm{No}\kern0.5em \mathrm{units}\kern0.5em \mathrm{PRCs}\times 168\right)/{\mathrm{Hct}}_{\mathrm{avg}}\right), $$

where$$ {\mathrm{Hct}}_{\mathrm{avg}}=\frac{\left({\mathrm{Hct}}_{\mathrm{pre}\hbox{-} \mathrm{op}}+{\mathrm{Hct}}_{\mathrm{post}\hbox{-} \mathrm{op}48\mathrm{h}}\right)}{2}. $$

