### Randomisation and blinding procedures

At the outset of the trial, eligible participants were allocated to intervention group 1, intervention group 2 or control group 3 (standard care) with an allocation ratio of 2:2:1. After the DMEC recommended stopping randomisation to control group 3, eligible participants were then allocated to intervention group 1 or intervention group 2 with an allocation ratio of 1:1. Blocked randomisation with randomly permuted block sizes is used. Participants are stratified according to operation type, surgeon and creatinine level, resulting in 16 possible stratifications (Fig. 3):

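### The protocol ties the primary outcome to analysis of variance and leaves adjustment optional; one ANCOVA with the stratification factors and baseline blood volume would give tighter intervals at no cost

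*Protocol article*

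**What the plan says.** Three parts of the protocol article bear on this.

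- **Analysis** (Statistical and interim analysis). The only method tied by name to the primary outcome is in this sentence: "For the primary outcome and other continuous outcomes, analysis of variance with contrasts will be used to compare both intervention groups". It goes on to contrast the two intervention groups together with control. The next sentence reads: "Analysis of covariance will be used to adjust for baseline and other covariates where appropriate". No covariate is named, and nothing says whether the adjusted or the unadjusted estimate is primary. The section adds "All analyses will be performed for THA and TKA separately and also combined" and "A statistical analysis plan will be written and approved prior to commencement of any analyses".
- **Randomisation** (Randomisation and blinding procedures). "Participants are stratified according to operation type, surgeon and creatinine level, resulting in 16 possible stratifications".
- **Outcome** (Primary outcome measure). "The first equation determines the patient’s blood volume in litres", from sex, height and weight. That volume is multiplied by the fall in haematocrit to give red cell loss, then divided by the average haematocrit. A transfusion term is added: "In addition, volume of transfused blood must be taken into account".

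**The concern.** Stratified randomisation balances operation type, surgeon and creatinine between the arms. If the model leaves them out, the variance they explain stays in the error term although it no longer contributes to chance differences between arms. The reported standard error is then too large and the test rejects slightly less often than 5% under the null.

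Separately, part of the outcome's spread is body size known before surgery. Patient blood volume multiplies the haematocrit change, and it must be computed for every participant to obtain the endpoint at all. A model without it gives up precision that is already available.

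Making adjustment conditional also leaves open which of two estimates is the primary one, in a trial whose investigators are not blinded.

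**Working it through.** **Inputs from the protocol article.** Mean 1225 mL, SD 499 mL, difference 150 mL, 90% power, significance level 0.05, 233 per TXA group for each joint, no allowance for dropout (Statistical and interim analysis). Four surgeons (Study setting) and 16 strata, hence 8 within a joint.

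**Assumed.** R², the share of outcome variance explained by baseline factors, is not given. I use 0.05 to 0.20.

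**1. The plan's own figure.** n per group = 2 × (1.96 + 1.2816)² × (499/150)² = 232.6, so 233. This is the two-sided result; a one-sided test would give 190. With 233 per group, SE = 499 × √(2/233) = 46.2 mL. Power = Φ(150/46.2 − 1.96) = 90.05%, and the 95% half-width is 1.96 × 46.2 = 90.6 mL. None of this uses a covariate.

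**2. Effect of adjustment.** Residual SD = 499 × √(1 − R²), put into the same formulas. The combined columns use 466 per group and also assume an SD of 499 mL.

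| R² | Residual SD (mL) | Power, one joint | Half-width, one joint (mL) | Power, combined | Half-width, combined (mL) |
|---|---|---|---|---|---|
| 0 | 499.0 | 90.05% | 90.6 | 99.6% | 64.1 |
| 0.05 | 486.4 | 91.4% | 88.3 | 99.7% | 62.5 |
| 0.10 | 473.4 | 92.8% | 86.0 | 99.8% | 60.8 |
| 0.20 | 446.3 | 95.2% | 81.0 | 99.9% | 57.3 |

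The intervals shorten by 1 − √(1 − R²): 2.5% at R² 0.05 and 10.6% at R² 0.20.

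**3. Is that range of R² plausible?** Ignore transfusion and suppose that the fraction of blood volume lost is independent of blood volume. Then R² from blood volume alone is (CV of blood volume / CV of loss)². The CV of loss is 499/1225 = 0.407. An assumed CV of blood volume of 10% gives (0.10/0.407)² = 0.06, 15% gives 0.14, 18% gives 0.195 and 20% gives 0.24.

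**4. How conservative is the unadjusted test?** Only the stratum variance matters here, because only the strata are balanced by design. If strata explain a share s, the true SE is √(1 − s) times the reported one, so the effective critical value is 1.96/√(1 − s). For s = 0.05 this is 2.01, a type I error of about 4.4%. For s = 0.10 it is 2.07, about 3.9%.

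A simulation of one joint agrees (8 strata, balanced allocation, 4,000 trials per scenario; assumed strata R² 0.05–0.10 plus covariate R² 0.10–0.20). Type I error was 3.8–4.3% unadjusted and 4.6–4.8% adjusted. Power was about 90–91% against 94–97%.

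**5. Recruitment period.** Groups 1 and 2 were allocated equally throughout (2:2:1, then 1:1). Control recruitment ended when 672 had been recruited, 134 of them controls. So 672 − 134 = 538 intervention participants are concurrent with control, and 932 − 538 = 394 of the minimum 932 (42%) come later.

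**The case against.** The strongest reply is that the text does not prescribe an unadjusted analysis. A reader might infer from the analysis-of-variance sentence that the primary model contains group alone. The documents do not support that: analysis of variance does not exclude stratum factors, and the following sentence provides for ANCOVA. Covariate lists also usually belong in the statistical analysis plan, which is promised and not shown. That stands, and the missing list is not the finding. What remains is that the protocol does state a method and makes adjustment conditional, where its own design and outcome formula support an unconditional commitment.

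A reader might also infer that the trial is short of power. It is not: the sample size was set on the full SD of 499 mL, and the planned power is met without any covariate.

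Three narrower replies also hold.

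- The separate hip and knee analyses already condition on operation type, so only surgeon and creatinine are left unmodelled there.
- The outcome is not strictly proportional to blood volume, because the transfusion term does not scale with it. This is minor: transfusion was 5.8% in knee patients at the site in 2013.
- The independence assumption behind the R² estimate is untested. The effect of body mass index on blood loss is itself a secondary outcome.

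**Conclusion.** The point holds as an efficiency improvement, not as an error of validity or a power shortfall. If the analysis is run as plain analysis of variance, the planned 90% power is met, the intervals are wider than necessary, and the test is slightly conservative.

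The gain from adjustment in a single joint is about 1 to 5 percentage points of power and roughly 2 to 10 mL of half-width. It depends on the assumed R² of 0.05 to 0.20. At the upper end, the chance of missing a true 150 mL difference in one joint falls from about 10% to about 5%. In the combined analysis, power rises by less than half a point and the benefit is precision.

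One might suppose that the mid-trial change in allocation confounds the main comparison. It does not, since groups 1 and 2 kept equal allocation before and after. Period matters only for the contrast with control.

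**What to change.** Replace the conditional wording with one primary model for group 1 versus group 2. This is an ANCOVA with treatment, surgeon and creatinine stratum, plus operation type in the combined analysis, and with baseline blood volume and pre-operative haematocrit as continuous covariates. Report the unadjusted analysis of variance as a sensitivity analysis. For the contrast of the combined intervention groups with control group 3 only, add a recruitment-period term, because control recruitment stopped early.

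The cost is wording, in the statistical analysis plan and in the protocol when next amended. The surgeon, operation and creatinine strata are known at randomisation, and the two covariates are already needed to compute the outcome. The sample size need not change.
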